**Research Summary**

**Principal Investigator:** [name] [name] PhD

**Co-Investigator:** [name]

1. **Protocol Title** – Physiological effect of sulforaphane obtained from brocoli sprouts homogenates (BSH) on the HbF and anti-oxidative capacity of human sickle red blood cells (SS RBC)
2. **Purpose of the Study** –

Primary Hypothesis: The reduced capacity to defend oxidative stress accounts for the accelerated hemolysis of SS RBC, but the causes for this defect are incompletely understood. We have analyzed microRNA in SS RBC and found that high miR-144 in SS RBC represses the protein and activities of NRF2, the master regulator of anti-oxidative capacity. In addition, low NRF2 then fails to repress expression of miR-144, forming a negative regulatory loop that maintains the high miR-144/low NRF2 in SS RBC. This dysregulation of miR-144-NRF2 is a critical sickle cell disease (SCD) feature likely to explain the reduced oxidative capacity. We propose to use sulforaphane homogenized from the commercially available fresh broccoli sprouts certified by Brassica Protection Products LLC, branded BroccoSprouts®, to activate NRF2 to restore anti-oxidative capacity and induce gamma and epsilon chain of the ß-like hemoglobins, which possess anti-sickling properties.

Secondary hypothesis: BroccoSprouts® homogenates (BSH) can be safely used in patients with SCD and may present a safe and effective means to induce HbF and enhance anti-oxidative stress capacity in SS RBC.

No Intent to Treat:

The study intends to determine physiologic effects of BSH on SS RBC but does not intend to treat.

**Specific Aims:**

[figure not shown]

Aim 1: Examine the in vitro response of HbAA and HbSS erythroid cells to NRF2 activation by sulforaphane. We will focus on the expression of anti-oxidative genes and HbF. In addition, we will use microRNA arrays to identify NRF2-responisve microRNAs to enable the comparison with erythrocyte microRNAs in Aim 3, and monitor NRF2 activation in erythrocytes. We seek to enroll 3 volunteers with Hb AA (normal) and 3 SCD subjects with Hb SS disease to donate blood for this study. The subjects will not receive any compensation for their participation. The labs and procedures describe in the Aim 2 baseline study visit will be performed in this Aim 1 study.

Aim 2: Perform a dose-escalation pilot trial (procedures described #4 and #5 below) of sulforaphane. We will recruit cohorts of SCD patients to receive escalating doses of sulforaphane to determine its influence on symptoms and laboratory values indicating safety, erythropoiesis, hemolysis and HbF levels.

Aim 3: Analyze the changes in the microRNA expression and anti-stress phenotypes of purified SCD erythrocytes after sulforaphane treatment. These changes, after comparing with the microRNA changes after in vitro treatment (Aim 1), will be used to identify microRNAs indicating NRF2 activation. We will also determine whether high erythrocyte miR-144, given their association with severe defective anti-stress capacity, may benefit more from sulforaphane treatment.

1. **Background & Significance** –

Sickle cell disease (SCD) is one of the most prevalent genetic disorders in the United States (US), affecting more than 80,000 people. SCD is an inherited hematological disease. The most common form of SCD is caused by homozygosity for the hemoglobin S (HbS) form of the β globin gene on chromosome 11. SS RBC has a dramatic reduction in the anti-oxidative stress capacity. Compared to normal RBC, SS RBC are constantly exposed to an increased level of oxidative stress to have higher demand for antioxidant capacity caused by the auto-oxidation and instability of sickle hemoglobin, increased xanthine oxidase, higher level of leukocyte NADPH oxidase. These higher levels of oxidative stresses are likely to contribute to the hemolysis in SCD and resulting cascade of pathological mechanism associated with free hemoglobin and sequestration of vasoactive NO. However, SS RBC has a significantly lower anti-oxidative capacity. This reduced antioxidant capacity is an important pathogenic mechanism rendering SS RBC susceptible to oxidative insult and hemolysis. While such reduce oxidative stresses in SS RBC is well recognized, the basis for such defect is not known.

Recently, we have found that this reduced oxidative stress capacity in SS RBC is partially due to reduced levels of NRF2 (Nuclear factor-erythroid 2-related factor 2) repressed by high miR-144 in SS RBC. NRF2 is a basic leucine zipper transcription factor that is a master regulator of the anti-oxidant stress responses of most mammalian cells. Under unstressed conditions, NRF2 interacts with Keap1, which sequesters NRF2 in the cytoplasm and maintains basal expression of NRF2-regulated genes. Upon exposure to oxidative stresses and various electrophilic molecules, NRF2 is released from Keap1 and translocates to the nucleus, where it binds to the antioxidant response element (ARE) found in the promoters of key genes involved in oxidative stress responses. NRF2-regulated expression of ARE-driven genes, especially those involved in the biosynthesis and recycling of glutathione (GSH), involved in protection against oxidative stress, are critical for survival during oxidative stress in various in vivo and in vitro models. Deletion of NRF2 leads to hemolytic anemia in murine models, indicating its importance in erythrocytes. Therefore, we reason that activation of NRF2 may repair the defect in the oxidative stress capacity and improve outcomes of SCD.

Given the importance of oxidative stress capacity, many compounds have been developed to induce NRF2 and build the capacity to defend oxidative stresses in different disease setting. For example, sulforaphane [1-isothiocyanato-4-(methyl-sulfinyl)butane] is a natural dietary isothiocyanate isolated from broccoli and other vegetables. Sulforaphane is found to be a very potent inducer of phase 2 detoxication enzymes and other anti-oxidative capacity in cultured cells and animal models. Sulforaphane has been found to possess potent anti-carcinogenic activities and has been used as a chemo-preventive agent to forestall the development of cancers.

**Preliminary Studies**: Gene expression studies with sulforaphane exposure has demonstrated that transcriptional responses that are caused by NRF2 induction because of the covalent modification of Keap1 on its 27 cysteine residues, thus allowing NRF2 to translocate to the nucleus. Although NRF2 induction and sulforaphane have been used to boost anti-oxidative capacity and prevent many diseases, such an approach has not been applied to anemia disorders. This gap is especially surprising, given that oxidative stresses have been recognized as critical factors in the hemolysis of SCD and other anemia disorders. Based on our findings of miR-144-repression of NRF2 as a cause of compromised anti-oxidative capacity in SS RBC, we are proposing to test the potential of NRF2 induction to boost RBC anti-oxidative stress capacity and improve hemolysis and gene expression under the high level of stress seen in SCD. We believe that NRF2 induction should be regarded as distinct from anti-oxidant supplementation, since it ensures that the HbSS RBCs have enough enzyme capacity to survive stress environments instead of simply providing anti-oxidant substrates to HbSS cells that are already handicapped by insufficient anti-oxidant machinery. Furthermore, NRF2 activation also leads to the induction of HbF and epsilon forms of Hb known to inhibit the HbS polymerization and exhibit anti-sickling properties. Therefore, NRF2 activation may simultaneously have multiple benefits to reduce the hemolysis of SCD and improve clinical outcomes.

1. **Design & Procedures** –

Study Type: This is an open label dose-escalation study to test the efficacy of daily intake of sulforaphane via broccoli sprout homogenates (BSH) to achieve the physiologically significant but non-clinical endpoint of induction of HbF, glutathione and anti-oxidative capacity in SCD erythrocytes. Each patient will serve as his/her own control, as all endpoints will be measured at pre-treatment baseline, during treatment of BSH, and post-treatment washout.

Study Population: HbSS and HbSßº thalassemia

Primary Endpoint: Safety

**Preliminary sulforaphane level measurement revised procedure:**

Because our previous methods for processing blood for Sulforaphane (SFN) metabolite detection were not adequate. Four SFN metabolites: SFN-Cys, SFN-CG, SFN-NAC and SFN-GSH, should be detected in all the processed samples, yet only SFN-NAC was detected in all samples, albeit at levels so low that the amount of this metabolite could not be accurately identified with the usual standards. SFN-Cys, SFN-CG, and SFN-NAC could not be detected in any of the samples. This preliminary work is to allow optimization of the dosing preparation and the sample collection method to ensure that the amount of sulforaphane obtained from our preparation will be adequate.

We will test the ability to measure the increase of sulforaphane levels after ingestion of the non-toxic sulforaphane in a shake, smoothie, or unprocessed fresh or thawed out frozen broccoli sprouts in 20 subjects (10 subjects with sickle cell anemia and 10 healthy controls). To assess these serum levels, we must use a detailed protocol to stabilize the naturally unstable sulforaphane metabolite, and this sample must later be measured by our collaborators at the Oregon State University ([name]). We must test the efficacy of our methods before proceeding with the main study to ensure that our detailed protocol is sufficient to stabilize the metabolite in the processed samples so that our collaborators at the Oregon Health can adequately test these metabolite levels.

Participants will be asked to donate three single blood samples by peripheral intravenous draw at about 30 minutes before ingestion, 4 hours after ingestion, and 6 hours after ingestion of 100, 150, or 200 grams of BroccoSprout® Homogenate (BSH). The maximum amount of blood that will be drawn is 10 ml at each time point for a maximum of 30 ml. Participants may be asked to repeat this procedure at different levels or preparation of BSH.

Secondary Endpoint: Physiological effects – HbF, GSH, anti-oxidative capacity and the expression of Phase II enzyme expression in SS RBC.

Projected Accrual: 50 patients for screening and 35 patients for participation in study.

COHORT 1 (5 patients) – Single 50 g BSH



Review by DSMB. If Board approves,



COHORT 2 (5 patients) – Single 100 g BSH



Review by DSMB. If Board approves,



COHORT 3 (5 patients)– Single 150 g BSH



Review by DSMB. If Board approves,



COHORT 4 (20 patients)– Single 200 g BSH

The 50 g BSH dosage may need to be adjusted to the minimal amount needed to have adequate Sulforaphane (SFN) metabolite detection.

If any serious adverse events occur, they will be reported immediately to the IRB. In addition, the study will be stopped until the DSMB reviews all available data and reaches a decision as to whether the study should be continued. The highest daily dose (200 mg) to be used in this study has been safely used in a previous trial. This dose will yield 102 μmol of sulforaphane. An escalating dose design is used in this study to monitor for safety in patients with sickle cell disease; also, previous studies show significant dose dependent increase on the response to BSH with greater response at the higher dose of 200 mg/day.

Study visits:

Screening/Baseline:

informed consent verification, medical history, review of concomitant medications, vital signs (VS), including height, weight, blood pressure, heart rate, pain, and fatigue. Venipuncture (up to 30 cc's) will be performed for CBC (complete blood count), LDH (marker for hemolysis), CMP (complete metabolic panel), baseline, hemoglobin electrophresis, HbF, Hb A2, SFN level, SFN-induced gene expression changes, RBC anti-oxidative capacity and gene expression.

Week 1 (Day 7): VS including height, weight, blood pressure, heart rate, pain, and fatigue, review of BSH intake (food diary) and concomitant medications, symptom/adverse event evaluation and continue food diaries; physical exam, vital signs (BP, pulse, temperature, height, weight, pain, and fatigue), review of concomitant medications. Venipuncture (up to 30 cc's) will be performed for CBC, LDH, SFN level. Review of food/fluids intake. Collection of sulforaphane supplement returned.

Week 2 (Day 14) VS including height, weight, blood pressure, heart rate, pain, and fatigue, review of BSH intake (food diary) and concomitant medications, symptom/adverse event evaluation and continue food diaries; physical exam, vital signs (BP, pulse, temperature, height, weight, pain, and fatigue), review of concomitant medications. Venipuncture (up to 30 cc's) will be performed for CBC, LDH, SFN level. Review of food/fluids intake. Collection of sulforaphane supplement returned.

Week 3 (Day 21): VS including height, weight, blood pressure, heart rate, pain, and fatigue, review of BSH intake (food diary) and concomitant medications, symptom/adverse event evaluation; medical history, review of concomitant medications, vital signs (VS), including height, weight, blood pressure, heart rate, pain, and fatigue. Venipuncture (up to 30 cc's) will be performed for CBC (complete blood count), LDH (marker for hemolysis), CMP (complete metabolic panel), baseline, HbF, SFN level, SFN-induced gene expression changes, RBC anti-oxidative capacity and gene expression.

Week 7 (Day 49, wash out): VS including height, weight, blood pressure, heart rate, pain, and fatigue, review of BSH intake (food diary) and concomitant medications, symptom/adverse event evaluation; medical history, review of concomitant medications, vital signs (VS), including height, weight, blood pressure, heart rate, pain, and fatigue. Venipuncture (up to 30 cc's) will be performed for CBC (complete blood count), LDH (marker for hemolysis), HbF, SFN level, SFN-induced gene expression changes, RBC anti-oxidative capacity and gene expression.

Participants while on the study will maintain a food diary. Each participant will receive instructions at the baseline visit on the use the food diary. The food diary data will be reviewed at each clinic visit.

The subjects who pass screening will receive sulforaphane in the form of broccoli sprout homogenates (BSH) for their intake at home daily for one week (plus 2 extra days’ supply). Subjects will return every week for the next 3 weeks of sequential visits.

1. **Selection of Subjects** –

*Inclusion Criteria*: Diagnosis of Hemoglobin (Hb) SS or Hb Sβ0 thalassemia by electrophoresis • Age ≥18 years • Hematocrit (Hct) ≥ 20% and Hb > 6.0 g/dL • Capacity to understand and sign informed consent and can adhere to the daily regimes of BSH

*Exclusion Criteria*: RBC transfusion during the 3 months prior to study entry • Pregnant• Currently receiving hydroxyurea treatments • Diabetes• Renal insufficiency (BUN >21 mg/dL and/or Creatinine >1.4 mg/dL) • History of allergy to sulfonamides

1. **Subject Recruitment and Compensation** – The consent process will occur in the Sickle Cell Center clinics at Duke South. All adult subjects may be approached for enrollment to the study if the inclusion criteria are met and they are patients. The PI or the research nurse will approach the potential participants. Participants will not receive any monetary compensation for their participation in the study.
2. **Consent Process** – Each subject must grant informed consent prior to enrolling in the study. No study procedure will be done prior to the patient consent. Participating subjects will be provided a copy of the dated and signed informed consent and the telephone numbers of the investigator and study personnel who can assist with any questions and or concerns.
3. **Subject’s Capacity to Give Legally Effective Consent** – Subjects will be 18 years, at of age or older and able to read and understand English.
4. **Study Interventions** – Prior to carrying out the procedure noted above in section #4, this study plans to recruit one subject to make sure that the methods for measuring blood serum Sulforaphane levels are adequate. We will test the ability to measure the increase of these levels after ingestion of the BSH shake for one student or employee. Nonparticipation or withdrawal from this study will not affect the student/employee's job status and nor grades. To assess these serum levels, a detailed protocol to stabilize the naturally unstable Sulforaphane metabolite will be used, and this sample will later be measured by our team of collaborators at the Oregon State University led by [name]. We must test the efficacy of our methods before proceeding with the study to ensure that our protocol is sufficient to stabilize the metabolite in the processed samples so that our collaborators at the Oregon Health can adequately test these metabolite levels. The student will be asked to donate three single blood samples by peripheral intravenous draw at about 30 minutes before ingestion, 4 hours after ingestion, and 6 hours after ingestion of one thawed-out shake containing 50 grams of BSH currently stored at the DCRU.

**Risk/Benefit Assessment** – The investigators of the study do not expect the participants to receive medical benefit from their participation in this study. The tests provided may help participants learn about your general health. However, information from this study may help the investigators learn things about sulforaphane’s physiological effect on SS RBC that will help other patients with sickle cell disease in the future. This is a minimally invasive study that poses a low risk to the subject other than the general risk of loss of privacy and insertion of a venous catheter for blood draw. BSH at the doses proposed in this study have been safely used in many clinical trials for a variety of disease. Sulforaphane has a good safety profile and has been approved as broccoli sprout tea or homogenate for several human clinical trials.

1. **Costs to the Subject** – There will be no cost to subjects to participate in this study. The study will pay for the research-related items or services that are provided.
2. **Data Analysis & Statistical Considerations** –

Sample size: 50 patients for screening and 35 patients for participation. Patients will be allowed to participate in more than one dose cohort. This is a pilot study. The in vivo study in Aim 1 is designed for the participation of 6 subjects.

Primary Endpoint: Measurement of the HbF, anti-oxidative capacity, GSH and phase II enzymes and microRNA gene expression before and after the BSH injection.

Secondary Endpoints: Safety data regarding use of BSH in patients with SCD.

Descriptive statistics will be used to characterize changes from baseline in laboratory test results.

1. **Data & Safety Monitoring** – A DSMB will be established for monitoring this clinical study. DSMB members, appointed by Drs. [name] and [name], will include at least three members with expertise in hematology or oncology. The DSMB will assess the risk of this clinical trial, determine the appropriate level of data and safety monitoring, review reports of all serious adverse events (SAEs), review the regularly submitted data and safety monitoring reports, and recommend appropriate actions (e.g. closure, increased monitoring) to the PIs.

All SAEs will be reported to the IRB, and the DSMB. The DSMB will review these data and notify the PI if safety appears to be an issue. If there are significant adverse events, the DSMB may recommend that the study be terminated. DSMB meetings for review of study data and decision of continuation will be scheduled as follows: after five patients complete the study at each dose level for cohort 1, 2, and 3; after twenty patients complete the study the 200 g dose level; or at any other times as deemed necessary by either the PI or any of the DSMB members.

1. **Privacy, Data Storage & Confidentiality** – The privacy rights of the subjects will be protected as required by law. All information that can identify an individual and the individual medical history will be kept confidential within the limits of the law. All study information will be kept locked in file cabinets accessible only by clinical research staff that are authorized and IRB-approved to participate in the study. Electronic information will be stored in secure electronic systems accessible only by Drs. [name] and [name], and their clinical research team.

Table 1. Study Related Tests and Procedures

| Procedures | Screening Visit | Baseline (Day 0) | Day 7 | Day 14 | Day 21 | Day 49  (Wash out) |
| --- | --- | --- | --- | --- | --- | --- |
| Informed Consent | X |  |  |  |  |  |
| Clinic Visit | X | X |  |  | X | X |
| Interview to identify AE’s |  | X |  |  | X | X |
| Vital Signs | X | X |  |  | X | X |
| Physical Examination | X | X |  |  | X | X |
| MD screen, history | X | X |  |  | X | X |
| BSH dispensed |  | X | X | X |  |  |
| **Clinical Laboratory Tests** |  |  |  |  |  |  |
| Venipuncture | X | X |  |  | X | X |
| Complete Blood Count (CBC) | X | X |  |  | X | X |
| Reticulocyte count | X | X |  |  | X | X |
| LDH (marker of hemolysis) | X | X |  |  | X | X |
| Comprehensive Metabolic  Profiling (CMP) |  | X |  |  | X |  |
| Hemoglobin electrophoresis |  | X |  |  |  |  |
| HbF quant |  | X |  |  | X | X |
| Serum SFN level |  | X |  |  | X | X |
| **Research Studies** |  |  |  |  |  |  |
| Glutathione |  | X |  |  | X | X |
| Anti-stress capacity |  | X |  |  | X | X |
| Reactive Oxygen Species |  | X |  |  | X | X |
| RBC/Reticulocyte RNA |  | X |  |  | X | X |
| PAXgene whole blood |  | X |  |  | X | X |

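### The preliminary assay study may give sickle cell subjects 100 to 200 g BSH before the DSMB approvals that the escalation plan requires for those levels, and Study Interventions describes a different preliminary study

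*Protocol*

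**What the plan says.** Under Design & Procedures, the subsection on the revised procedure for measuring sulforaphane plans preliminary work "in 20 subjects (10 subjects with sickle cell anemia and 10 healthy controls"). Blood is drawn about 30 minutes before, 4 hours after and "6 hours after ingestion of 100, 150, or 200 grams of BroccoSprout® Homogenate (BSH"). Repeats are allowed: "Participants may be asked to repeat this procedure at different levels or preparation of BSH". The timing is explicit: "We must test the efficacy of our methods before proceeding with the main study".

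The same part of the protocol then sets out the main study: cohorts of 5, 5, 5 and 20 patients at 50, 100, 150 and 200 g, with DSMB review and approval between each cohort and the next. The reason given is: "An escalating dose design is used in this study to monitor for safety in patients with sickle cell disease". Data & Safety Monitoring schedules DSMB meetings after five completers in each of cohorts 1 to 3 and after twenty at 200 g. It also allows meetings at other times if an investigator or a DSMB member thinks one necessary.

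Study Interventions gives another account of the preliminary work: "this study plans to recruit one subject to make sure that the methods for measuring blood serum Sulforaphane levels are adequate". That subject is a student or employee, and the exposure is "ingestion of one thawed-out shake containing 50 grams of BSH currently stored at the DCRU".

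On the first cohort's level, Design & Procedures adds: "The 50 g BSH dosage may need to be adjusted to the minimal amount needed to have adequate Sulforaphane (SFN) metabolite detection".

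**The concern.** An escalation scheme protects patients by the order in which levels are reached and by the review required before each step up. Here the preliminary phase can take sickle cell subjects straight to the three levels that the main study holds behind DSMB approval, before the lowest cohort has opened. Because repeats are allowed, one subject could take more than one of those levels, and no order, interval or review between them is stated.

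Two things add to this. The two accounts of the preliminary work cannot both be followed, so site staff and the DSMB cannot tell who is to be exposed and at what level. And the 50 g starting level may be changed for assay reasons, but the protocol does not say which preliminary results decide the change, or how the changed level relates to the 100 g cohort that follows. At stake are the meaning of the DSMB approvals and the completeness of the safety record in a study whose Design & Procedures section names safety as the primary endpoint.

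**Working it through.** The check is mainly a comparison of sections, with a little arithmetic.

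**Step 1: the plan's own accrual figure.** Cohort sizes: 5 + 5 + 5 + 20 = 35, which matches the stated 35 participants. The 35 is thus used up by the cohorts, and the preliminary subjects are not counted in it. If nobody takes part twice, adding the 10 preliminary sickle cell subjects gives 35 + 10 = 45, and adding all 20 preliminary subjects gives 35 + 20 = 55.

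**Step 2: order of exposure in sickle cell subjects.**
- Escalation scheme alone: before the first scheduled DSMB meeting, 5 patients have taken 50 g and 0 have taken more.
- With the preliminary study done first: up to 10 have already taken 100, 150 or 200 g.
- Ratio to the cohort 1 amount: 100/50 = 2 at the lowest preliminary level and 200/50 = 4 at the highest.
- All three levels that need DSMB approval in the main study are among the preliminary levels. The text does not allocate levels between sickle cell subjects and controls, so 10 subjects and three levels are maxima.

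**Step 3: oversight of the preliminary phase.**
- Scheduled DSMB meetings: four points (after cohorts 1, 2 and 3, and after the 200 g cohort). None is tied to the preliminary phase.
- Adverse event assessment: the preliminary subsection lists three blood draws and nothing else. Table 1 has adverse event interviews at baseline, Day 21 and Day 49 of the main study and no column for the preliminary phase. The visit descriptions likewise concern the main study only.
- Other provisions: a serious adverse event stops the study until the DSMB has reviewed it, and ad hoc meetings are possible. The first acts after an event and the second is optional. Neither is approval before a level is given.

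**Step 4: the two preliminary studies side by side.**

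| Item | Revised measurement procedure | Study Interventions |
| --- | --- | --- |
| Subjects | 20 | 1 |
| Population | 10 sickle cell, 10 healthy | one student or employee |
| BSH amount | 100, 150 or 200 g | 50 g |
| Preparation | shake, smoothie, or fresh or thawed sprouts | one thawed shake |
| Repeats | allowed | not mentioned |
| Sampling times | 30 min before, 4 h and 6 h after | the same |
| Timing | before the main study | before the main study |

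The accounts agree on purpose, timing and sampling. They differ in size and population and share no dose level.

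**Step 5: the adjustable 50 g level.** The sentence allowing the change names a criterion (adequate metabolite detection). It names no data source and no upper limit, and it does not mention the next cohort at 100 g. Of the two preliminary accounts, only the one in Study Interventions includes 50 g.

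**The case against.** Much can be said for the plan. The preliminary exposure is an ingestion followed by a few hours of sampling, whereas the visit schedule describes daily intake at home over three weeks. If the cohorts are read as daily dosing, the DSMB approvals still control multi-week exposure at every level. A reader might infer that the escalation is defeated altogether; the documents do not support that. The objection stands to this extent: the bypass concerns dose level, not duration. It does not remove the point, because the approvals are written by dose level and the cohort lines themselves describe each amount as single.

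Oversight is not absent. Serious adverse events stop the study and go to the IRB and DSMB, and the DSMB may meet when it sees fit and is to set the level of monitoring. That is correct, so the claim is limited to the lack of a scheduled review and of any listed adverse event assessment in this phase.

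The protocol also describes BSH at these doses as safely used in earlier trials. But it says that this approach has not been applied to anemia disorders, and it states the previously used top dose in milligrams while the cohorts are in grams. It also judged escalation necessary for safety in this population despite that experience.

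The Study Interventions text may be a leftover, since the other account is headed as revised and calls the previous processing methods inadequate. That is plausible, but the section is written as a current plan and nothing marks it as replaced.

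Two further inferences are tempting and should not be drawn. One is that the preliminary work can say nothing about 50 g: Study Interventions tests exactly that level, and a failure to detect metabolites at 100 g would also count against 50 g. The other is that earlier exposure spoils the cohort comparisons: cohort entrants have their own baseline visit, and the protocol openly lets patients join more than one dose cohort.

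**Conclusion.** The point holds for dose level and for the consistency of the protocol. Up to 10 sickle cell subjects may take 2 to 4 times the cohort 1 amount before the first scheduled DSMB meeting, against 0 under the escalation scheme alone, in a phase with no scheduled DSMB review and no listed adverse event assessment. Separately, two current sections describe incompatible preliminary studies (20 subjects at 100 to 200 g against 1 subject at 50 g), and the change to the 50 g level is tied neither to named data nor to the cohort sequence.

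This rests on two readings: that the preliminary study is completed before cohort 1, as the text says, and that its sickle cell subjects may be given any of the three listed levels, which the text does not exclude. A reader might want a probability of harm. The documents give no reaction rate for these levels, so none is offered, and the conclusion does not need one. No view is taken on which level, population or clinical rule is right.

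**What to change.** Amend the protocol so that the preliminary measurement subsection, the rest of Design & Procedures, Study Interventions, and Data & Safety Monitoring agree:

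- Describe one preliminary study, with one size, population, set of levels and rule on repeats, and remove the other account.
- Reconcile the levels planned for sickle cell subjects in that study with the escalation and the DSMB schedule that the protocol already sets. How this is done is for the sponsor, the investigators and the DSMB.
- Say which preliminary data inform any change to the 50 g level, and make that provision consistent with the cohort sequence.
- Record adverse events in the preliminary phase, show this in Table 1 or a companion table, and include the results in the DSMB's review, stating at which meeting.
- State whether preliminary subjects count towards the accrual of 35.

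The cost is a protocol amendment and possibly some delay to assay work in sickle cell blood. No extra patients are needed.

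### The metabolic panel (CMP) is not repeated at the Day 49 wash-out visit, so a Day 21 kidney or liver chemistry change has no scheduled follow-up value

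*Protocol*

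**What the plan says.** Protocol, Design & Procedures, Study Type: each patient is his or her own control, and "all endpoints will be measured at pre-treatment baseline, during treatment of BSH, and post-treatment washout". Safety is then named as the primary endpoint. Data Analysis & Statistical Considerations lists it as secondary.

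Protocol, Study visits, blood tests by visit:

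- Screening/Baseline includes "LDH (marker for hemolysis), CMP (complete metabolic panel), baseline, hemoglobin electrophresis, HbF, Hb A2, SFN level".
- Day 7 and Day 14: "Venipuncture (up to 30 cc's) will be performed for CBC, LDH, SFN level".
- Week 3 (Day 21) includes "LDH (marker for hemolysis), CMP (complete metabolic panel), baseline, HbF, SFN level".
- Week 7 (Day 49, wash-out) orders CBC, then "LDH (marker for hemolysis), HbF, SFN level, SFN-induced gene expression changes, RBC anti-oxidative capacity and gene expression".

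Protocol, Table 1: the CMP row reads "Profiling (CMP) | | X | | | X", that is, Baseline (Day 0) and Day 21, with Day 49 blank. The venipuncture row reads "Venipuncture | X | X | | | X | X", so blood is drawn at Day 49. The dispensing row reads "BSH dispensed | | X | X | X".

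Protocol, Data & Safety Monitoring: the DSMB reviews the data once five patients have completed the study in each of cohorts 1 to 3, and again after twenty patients at the highest level.

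**The concern.** The Day 21 and Day 49 test lists run in parallel, except that the Day 21 list has CMP between LDH and HbF and the Day 49 list goes straight from LDH to HbF. No other scheduled test would show kidney or liver chemistry. Kidney function matters to this protocol, since BUN and creatinine limits are exclusion criteria, and Aim 2 looks to laboratory values for evidence of safety.

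There is no parallel control arm. The wash-out value is therefore the only scheduled way to see whether a change found at the end of intake persists or resolves. Without a Day 49 CMP, a raised creatinine or liver test at Day 21 has no scheduled repeat, and the DSMB would judge the next dose level without knowing which of the two happened.

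**Working it through.** No power, alpha or sample-size figure is involved. The check sets the two schedules side by side and counts.

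**1. Where CMP is ordered**

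| Visit | Visit text: blood drawn | Visit text: CMP | Table 1: venipuncture | Table 1: CMP |
| --- | --- | --- | --- | --- |
| Screening | yes (combined with baseline) | yes (combined) | yes | no |
| Day 0 | yes (combined with screening) | yes (combined) | yes | yes |
| Day 7 | yes | no | no | no |
| Day 14 | yes | no | no | no |
| Day 21 | yes | yes | yes | yes |
| Day 49 | yes | no | yes | no |

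Post-baseline CMPs are 1 of 4 post-baseline draws by the text (Days 7, 14, 21, 49), and 1 of 2 by Table 1 (Days 21, 49). After treatment there are 0 by either source. The text and the table disagree on whether blood is drawn at Days 7 and 14, which needs reconciling separately. It does not change this count, because neither places a CMP on those days.

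**2. What is repeated at Day 49.** CBC and LDH are ordered in both text and table, and reticulocytes in Table 1. HbF, serum sulforaphane and the research assays are also repeated. Hemoglobin electrophoresis is not, but it serves diagnosis rather than safety. CMP is thus the one repeated safety laboratory test without a wash-out value.

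**3. When treatment ends.** The protocol gives no last treatment day. Supplies are dispensed on Days 0, 7 and 14, each for one week of daily intake plus two spare days.

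- Planned end: 14 + 7 = about Day 21.
- If the spare days of the last supply were also used: 14 + 9 = about Day 23.
- Wash-out length: 49 − 21 = 28 days, or 49 − 23 = 26 days.
- Interval from the last scheduled CMP to the last visit: 49 − 21 = 28 days in either case.

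**4. What the DSMB would have.** Cohort places: 5 + 5 + 5 + 20 = 35. If completing the study means attending Day 49:

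| Review | Post-baseline CMPs as written | With a Day 49 CMP |
| --- | --- | --- |
| Each of cohorts 1, 2, 3 | 5 × 1 = 5, none after treatment | 5 × 2 = 10, 5 of them at wash-out |
| Cohort 4 | 20 × 1 = 20, none after treatment | 20 × 2 = 40, 20 of them at wash-out |

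Under that reading, each Day 21 value is at least 28 days old at the review.

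**The case against.** The strongest reply is that text and table agree, so the omission is consistent and may be deliberate. The sentence just before the promise about all endpoints describes the aim as induction of HbF, glutathione and anti-oxidative capacity, all of which are marked at Day 49. Nowhere is the safety endpoint defined as CMP. This stands: a reader might infer that the protocol contradicts itself, but the documents do not go that far. What remains is a poor fit between a broad promise, safety named as primary in the same section, and a safety panel with no wash-out value.

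A reader might also infer that recovery is never checked. That is too strong. Table 1 schedules an adverse event interview, physical examination, vital signs, CBC, reticulocytes and LDH at Day 49. The DSMB can recommend increased monitoring and can meet outside the planned times. Only scheduled chemistry is missing. Tests ordered on request could fill the gap for individual patients but would not give a systematic series. A patient who enters a further cohort would have a new baseline CMP, but re-entry is optional.

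Third, Day 21 is about the end of exposure and so the more informative point for detecting a chemistry effect, and it is covered. With five patients per lower cohort and no control arm, a Day 49 value cannot by itself separate an effect of the sprout homogenate from chance variation. That is correct, and the case for the test should not rest on it.

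Finally, this is a descriptive pilot of a product the protocol describes as low risk. That limits the weight of the point but does not supply the missing value.

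**Conclusion.** The point holds as a modest gap in the safety schedule. Each course has two scheduled CMPs, one before treatment and one at Day 21, and none in the 28 days to the final visit, although blood is drawn there. Each lower-dose DSMB review would have one post-baseline CMP per patient and no scheduled chemistry recovery data.

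This rests on four assumptions:

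- CMP has its usual kidney and liver content, since the protocol does not list its components.
- Treatment ends at about Day 21, inferred from dispensing. The cohort list describes single amounts while the visit section describes daily intake at home, and those passages must be reconciled.
- Completing the study means attending Day 49.
- The promise about all endpoints extends to safety. If it covers only the physiological endpoints, the point is no longer a misfit with the protocol's own rule, but it remains a worthwhile and cheap improvement.

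Sample size, error rates and the physiological endpoints are not affected. The change should be made, but nothing here shows the trial to be unsafe or its main measurements invalid.

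**What to change.** In Study visits, Week 7 (Day 49), insert CMP between LDH and HbF, as in the Week 3 list, and mark the Day 49 cell of the CMP row in Table 1. In Data & Safety Monitoring, state that the data for each cohort review include the Day 21 and Day 49 CMP, and say whether completing the study means the Day 49 visit.

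The cost is one routine assay per cohort place, at most 35, on blood from a draw already scheduled (up to 30 cc), plus a minor amendment. No extra visit or venipuncture is needed. The gain is that each course has three scheduled CMPs instead of two, and a Day 21 change can be seen to persist or resolve.
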